## Trial status

The trial was registered in ISRCTN, number of identification 56784470. Date of registration: 27 October 2022. The study is currently using trial protocol version 4.0 dated 31st May 2024. Recruitment commenced in July 2023 and is ongoing and due to close within academic year 2024–2025. Data collection will end 4 months later.

## Discussion

There has been growing evidence for increasing prevalence of anxiety and depression amongst university students [1–5]. These common mental health problems are associated with lower academic grades and higher rates of drop-out from university as well as predicting negative impact on future careers. Critically, most students who experience anxiety and depression do not receive evidence-based interventions [6–10]. As such, there is an onus to determine scalable, feasible, and efficacious interventions and to appropriately direct students to the appropriate intervention.

Digital CBT provides one potential route to increasing coverage of efficacious interventions and is increasingly being offered as part of the portfolio of mental health services within UK universities, albeit often in an unguided format. It is therefore of great value to know the relative efficacy of guided versus unguided i-CBT for anxiety and depression in university students as well as to distinguish the subsets of students that are as responsive to self-guided as guided i-CBT, responsive only to guided i-CBT, and unresponsive to either and requiring further stepping up to higher intensity psychological therapy. Identifying an ITR is a key step towards precision treatment personalization and to prepare for definitive trials that test whether treatment allocation using ITRs improves outcomes relative to random allocation or usual practice.

The proposed comparison of guided vs unguided digital CBT is the most useful from a service delivery and cost-effectiveness perspective as it is the one with greatest implications for university wellbeing services implementation. Similar i-CBT packages are increasingly becoming a routine offer in UK universities, without knowing if they are being offered to the right students or if supported versions would do better if targeted appropriately. In the context of both increasing mental health demand in universities and constrained finances in higher education institutions, a better understanding of what works and for whom has considerable potential for impact in helping to develop more personalized and cost-effective services.

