## Abstract

**Background:**

Tackling poor mental health in university students is a priority in higher education. Although major depressive disorder and generalized anxiety disorder are highly prevalent among university students and predict impaired university and later life outcomes, most students do not receive evidence-based treatment. Internet-delivered cognitive-behavioural therapy (iCBT) is increasingly offered to UK university students in guided or unguided formats. Our aim is to compare the effects of guided versus unguided scalable iCBT for university students with elevated symptoms of depression and/or anxiety and to investigate the feasibility of creating individual treatment rules (ITR) to predict for whom which variant of iCBT is more effective as well as for whom neither is effective.

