A key uncertainty within digital self-help is the heterogeneity of treatment effects; that is, variations in individual treatment response to different treatments [19, 24]. Understanding which digital self-help interventions are most acceptable and work best for which students could help to tailor self-help interventions, plan the care pathway, and improve outcomes. A critical question is how much and what kind of support from a practitioner is needed: unguided self-help has greater reach, sustainability and scalability as it is not limited by therapist capacity, opening up the potential for massive cost-effective open online interventions [26] but may have less engagement and efficacy than guided interventions [17, 20, 24, 25, 27, 28], although there is some heterogeneity [19, 24], with a subset of individuals benefiting as much from unguided self-help as guided self-help [25, 29]. Identifying such a subset would be of enormous value in increasing treatment scalability.

An emerging approach to develop precision predictive models is to use machine learning. A recent study used this approach to develop individualized treatment rules (ITR) for university students with anxiety or depression in Mexico and Colombia who had participated in a pragmatic trial comparing guided iCBT versus unguided iCBT versus treatment-as-usual [27, 30]. Machine learning enables the estimation of a prediction model for each treatment arm, which can then be used to determine counterfactual predicted outcomes for each student for guided i-CBT relative to unguided i-CBT and then to compare the difference between each predicted outcome to decide which treatment is best for each student. Such information could be very useful for deciding what type of treatment to offer different types of students and for planning of student treatment services.

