### Objective

The primary objective is to examine the aggregate efficacy of guided transdiagnostic i-CBT relative to unguided i-CBT to reduce symptoms of depression and anxiety over a 3-month period in university students who report elevated depression and/or anxiety, as operationalized by caseness on well-established self-report measures. As noted above, we know from much previous research that the aggregate efficacy of guided i-CBT is likely to be significantly higher than that of unguided i-CBT. A secondary objective is to use machine learning methods to predict heterogeneity of treatment effects of unguided iCBT versus guided iCBT and develop ITRs to predict which students will respond as well as, or possibly even better than, to self-guided as to guided i-CBT.

We hypothesize that consistent with prior findings [17, 20, 24, 25, 27, 28], for university students with elevated depression and/or anxiety, the guided i-CBT will outperform unguided i-CBT in the aggregate in reducing symptoms of depression and anxiety across 3 months. We further hypothesize that a small subset of users will benefit at least as much from unguided as from guided i-CBT and that we will be able to identify this subset of students prior to randomization using machine learning methods [30]. Importantly, we also anticipate that some proportion of students will fail to improve meaningfully with either guided or self-guided i-CBT and that we will be able to identify this segment of the population with good accuracy using the same machine learning measures as those used to develop the ITR. If so, this information could be used to refer such students to more intensive care rather than requiring them first to fail as a course of i-CBT.

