### Study design

The trial design is a superiority parallel 2-arm individual-level single-blind (with researchers following up participants and statisticians conducting analysis blind to treatment allocation) randomized controlled trial (RCT). All participants will be randomized with equal allocation to receive either guided or unguided i-CBT.

Potential participants for the trial will provide initial consent to complete screening measures to determine if they are eligible to participate in the trial, i.e. showing elevated anxiety and/or depression or current diagnosis of major depression. Any potential participants who are found not to be eligible will automatically be signposted to other sources of support. Once trial eligibility has been determined and consent to participate in the trial has been obtained, participants will be individually selected at random (in a 1:1 ratio) to be offered guided i-CBT or unguided i-CBT.

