For the purposes of precision models, we will first explore which pre-treatment measures moderate the differential effects of treatment condition. Because individual predictors are usually weak and underpowered, our primary approach will be to use composite models that combine individual moderators to produce ITRs that can guide the selection of treatments most likely to be helpful for individual students. The approach will follow precedents established for developing precision treatment models via cross-validated machine learning methods as used in similar studies [30, 59–61]. Such machine learning methods for estimating heterogeneity of treatment effects include extensions of the generalized random forest algorithm [62–64] and of the Super Learner algorithm [65, 66], an ensemble machine learning approach. We will use the generalized random forest algorithm [62–64], with the option to add machine learning approaches (including ensemble approaches) as necessary, to develop a model that best predicts the relative effectiveness of alternative interventions. The machine learning approach has been validated for developing effective composite models, e.g. developing preliminary ITR with *n* = 150 [57, 61] and has the advantages of avoiding the need to specify main effects correctly and allowing the data‐driven estimation of nonlinear and higher‐order complex interactions across predictors. The value of guided and unguided iCBT at the individual level will be quantified using a counterfactual approach estimating the attained improvement of the mean outcome under a treatment selection scheme that always selects the treatment option with the best predicted outcome compared to the mean outcome under balanced randomization, generating a difference score or a personalized advantage index [67].

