Secondary analysis will be undertaken including:Complier Average Causal Effect (CACE) analysis [68, 69] to provide an estimate of a treatment effect accounting for pre-specified per-protocol adherence and compliance with the treatment, whilst retaining the benefits of randomization.The extent of missing data will be considered, and where necessary, in agreement with the Trial Steering Committee (TSC), imputation (e.g. doubly robust estimation combining propensity score models with multiple imputation to reduce risk of bias) will be used to adjust for loss to follow-up.Exploratory mediation analyses will be undertaken to gain insight into mechanisms that could explain the potential effect of the interventions on primary outcomes. We will use modern causal inference methods using structural equation modelling or parametric regression models to assess mediation effects [70]. For mediation analyses of longitudinal data, assuming ICC = 0.5, the sample sizes to achieve MCID calculated above can detect small effect sizes for mediators (β = 0.14) in RCTs (with up to 8 micro-repeated assessments), at power = 0.80. A series of models will be performed for each outcome, investigating the mediation effect of each mediator variable individually and the mediation effect of each mediator variable in an overall model combining all mediators. The mediation effect will be reported as the indirect effect of treatment via the specified mediator, with a 95% confidence interval and the proportion of the total intervention effect mediated. Analyses will include the use of instrumental variables to account for effects of unobserved confounding on mediators [68].In addition, the ITR analysis will include composite baseline predictors estimated using nested cross-validation machine learning methods, to assign each participant a predicted probability of adherence to self-guided i-CBT and a separate predicted probability of adherence to guided i-CBT. The use of such composite measures as predictors in developing the ITR will make it possible to distinguish heterogeneity in treatment effects due to predicting differential adherence versus differential effectiveness of the two interventions given adherence.The results of all models will be compared to primary analysis complete case ITT results.

Analyses will be undertaken by a statistician blinded to group allocation and using Stata v.17 and R 4.5.0.

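### With two active arms, the trial can predict who does poorly under both i-CBT versions, but not for whom neither works; the adherence split needs assumptions the protocol does not state

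*Protocol article*

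**What the plan says.** The comparison has two active arms. Under Study design: "All participants will be randomized with equal allocation to receive either guided or unguided i-CBT". No untreated, usual-care or higher-intensity arm is described.

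The group that neither version helps is worded in three ways:

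- Abstract, Background, as part of the aim: predict for whom which variant is more effective, "as well as for whom neither is effective".
- Objective, as a hypothesis: "some proportion of students will fail to improve meaningfully with either guided or self-guided i-CBT". The authors expect to identify this segment with good accuracy and add, conditionally, that "this information could be used to refer such students to more intensive care".
- Discussion, among the things of value to know: students "unresponsive to either and requiring further stepping up to higher intensity psychological therapy", listed beside a group that responds to the guided version alone.

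The planned analysis is built on arm-specific predictions. The Background explains that "Machine learning enables the estimation of a prediction model for each treatment arm". The Statistical analysis plan section values the rule by a scheme that always "selects the treatment option with the best predicted outcome compared to the mean outcome under balanced randomization".

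On adherence, the same section plans composites of baseline predictors that give each participant one predicted probability of adherence per arm. It states, without qualification, that using these as predictors will allow the analysis to "distinguish heterogeneity in treatment effects due to predicting differential adherence versus differential effectiveness of the two interventions given adherence". Under Intervention adherence, compliance is completion of at least 4 of the 8 core modules.

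**The concern.** The abstract and Discussion wordings are causal. To say that neither version is effective for a student is to say that the outcome would have been no worse without i-CBT. To say that the student requires a step-up is to say that a more intensive therapy would do better. The design observes neither comparator. Students whom i-CBT keeps from worsening would look the same as students on whom it has no effect, and both could be reported as unresponsive. The Objective links this group to possible referral elsewhere, so the label matters.

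The adherence statement has a different fault. Adherence arises after randomization and can occur in both arms. Effectiveness given adherence is therefore a contrast within a latent group, such as students who would adhere under either version. A score computed from baseline covariates does not reveal who those students are. If the split were reported as a plain result, readers could take an assumption-dependent quantity for a finding protected by randomization.

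**Working it through.** The protocol gives no figure to reproduce here. The question is what the design identifies, so it is checked by potential-outcome reasoning and two constructed examples. All values in the examples are assumptions.

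**1. What two arms identify.** Write X for the baseline profile and Y(g), Y(u), Y(0) for the 3-month change under guided i-CBT, unguided i-CBT and no i-CBT. Randomization identifies E[Y(g)|X] and E[Y(u)|X], and so their difference. Nothing in the trial informs E[Y(0)|X] or the outcome under a higher-intensity therapy. It follows that:

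- poor predicted outcome under both arms (Objective wording) is estimable, for students of a given profile though not as one student's pair of responses;
- neither version effective (abstract wording) needs E[Y(g)-Y(0)|X] and E[Y(u)-Y(0)|X], which are not estimable;
- requiring a step-up (Discussion wording) needs an arm that does not exist.

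**2. Constructed example, PHQ-9 change (negative is improvement).** Effect = change in the arm minus untreated change.

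| Subgroup | Guided | Unguided | Untreated (assumed) | Guided effect | Unguided effect |
|---|---|---|---|---|---|
| A, case 1 | -0.5 | -0.5 | +4 | -0.5 - 4 = -4.5 | -4.5 |
| A, case 2 | -0.5 | -0.5 | -0.5 | 0 | 0 |
| B, case 1 | -6 | -4 | -4 | -6 + 4 = -2 | 0 |
| B, case 2 | -6 | -4 | 0 | -6 | -4 |

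Within each subgroup the trial data are the same in both cases. Subgroup A looks unresponsive to either version, yet the effect may be substantial or nil. Subgroup B shows that responding to the guided version alone is ambiguous in the same way: the unguided effect is 0 in one case and -4 in the other.

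**3. Constructed example, adherence.** Assume that anyone who would adhere unguided would also adhere guided. Let 30% adhere under both versions, 30% under guided only and 40% under neither. Suppose guided adherers average -6 and unguided adherers -5.

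- Unguided adherers are all from the adhere-under-both group, so that group's unguided mean is -5.
- Guided adherers are an equal mix of two groups, so (0.3a + 0.3b)/0.6 = -6, where a is the guided mean of the adhere-under-both group and b that of the guided-only group. Hence b = -12 - a.
- The effect given adherence under both versions is a - (-5) = a + 5.

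| a | b = -12 - a | Effect = a + 5 |
|---|---|---|
| -4 | -8 | +1 |
| -5 | -7 | 0 |
| -6 | -6 | -1 |
| -7 | -5 | -2 |
| -8 | -4 | -3 |

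Every row fits the same adherence rates and the same means among adherers. Even the sign is open. Principal ignorability (here a = b, in general conditional on X) selects the row with effect -1, but the data cannot test it. The predicted probabilities are functions of X. They show how the total effect varies with predicted adherence, but do not choose among the rows.

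**The case against.** A fair defence has four parts.

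First, the Objective already defines the group by failure to improve meaningfully under either version. That is a prognostic statement, estimable from two arms and of possible use for triage. This stands. It rules out the stronger reading that no such group can be identified at all.

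Second, the Discussion sentence is a remark on what would be valuable to know, the abstract speaks of investigating feasibility, and the rule itself is valued only relatively, one arm against the other. This also stands and limits the weight of the point. It does not repair the abstract, where the causal wording is part of the stated aim. Nor does the precedent help: the Background says that the Mexico and Colombia trial included a treatment-as-usual arm, which this trial lacks.

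Third, arm-specific adherence models are a usual input to principal-score methods, so the split can be estimated under principal ignorability or a similar assumption, and an analysis plan that is not shown may state one. Adherence after randomization is not ignored either: a CACE analysis and mediation with instrumental variables are planned. This stands against any claim that the split is impossible. It does not support the flat statement in the article, which presents the composites themselves as sufficient.

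Fourth, a reader might infer that the adherence split is meant to decide who bypasses i-CBT. The text does not say so: referral is mentioned only for the group that fails to improve, and conditionally. A reader might also want a figure for how much apparent improvement is natural recovery or regression to the mean. The article gives no baseline means or test-retest correlations from which to derive one.

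**Conclusion.** The point holds in a limited form. The design supports a group with predicted poor 3-month outcome under both arms. It does not support the statements that neither version is effective for that group, that its students need a step-up, or that some students respond to the guided version alone in any sense beyond the guided-unguided contrast. A larger sample or a different learner would not change this, because the missing comparator is a matter of design.

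The adherence statement is too strong as written. Effect modification by predicted adherence is identified; effectiveness given adherence is identified only under untestable assumptions.

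The examples use assumed values. They show that the quantities are not determined by the data, not how far they would vary in this trial. What is affected is the conclusions the trial may draw from the rule. The primary comparison, allocation, sample size, data collection and relative valuation of the rule are untouched.

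**What to change.** In the abstract and Discussion, use the sense of the Objective: *predicted poor 3-month outcome under both arms (prognostic)*. Evaluate that group by calibration and discrimination of the arm-specific predictions. State that no inference is drawn that i-CBT is ineffective for these students or that a more intensive therapy would help them. Describe the group said to respond to the guided version alone in terms of the guided-unguided contrast. The referral sentence in the Objective and the step-up wording in the Discussion should be reconciled with this.

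In the Statistical analysis plan section, either report predicted adherence as a candidate moderator only, or present the decomposition as exploratory, name its assumptions (for example monotone adherence and principal ignorability), and add a sensitivity analysis that varies them.

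The cost is wording, plus the sensitivity analysis if the decomposition is kept. No design, data or sample-size change is needed; the claims become more modest.

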## Data Availability

Anonymized datasets arising from this trial will be made available after the primary outcomes are published to researchers and other groups via request to a data committee within the trial consortium and via an open access repository. The results will additionally be updated on https://www.isrctn.com/ISRCTN56784470. We plan to communicate trial results through peer-reviewed open access publications and direct reports to TSC, sponsor, and participants.

## Abbreviations

AE: Adverse event
CACE: Complier average causal effect
DMC: Data Monitoring Ethics Committee
DSM-V: Diagnostic and Statistical Manual of Mental Disorders, Fifth Edition
EDC: Electronic Data Capture System
ExeCTU: University of Exeter Clinical Trials Unit
GAD-7: Generalized Anxiety Disorder-7
ITR: Individualized treatment rule
ITT: Intention-to-treat
MDD: Major depressive disorder
MI: Multiple imputations
NHS: National Health Service
NIHR: National Institute for Health Research
NRES: NHS National Research Ethics Service
PHQ-9: Patient Health Questionnaire
PIS: Participant Information Sheet
PWP: Psychological Wellbeing Practitioner
RCT: Randomized controlled trial
SAE: Serious adverse event
TSC: Trial Steering Committee
